### Covariates

The following covariates will be considered in comparing intervention effectiveness outcomes between the intervention arms: age, socio-economic status, family structure, family support, marital status, living arrangements, employment status, and neighborhood safety nets and assets.

### Sample size and sample selection

Aside from using the pilot study to assess the feasibility and implementation of the intervention, we also aim to ensure that the pilot study provides us with preliminary data to accurately estimate the sample size for a fully-fledged intervention study in the future. That is, we expect the pilot data to enable accurate estimation for the within-group variance, intraclass correlation, and estimate of true effect size for a larger study. Thus, we approach the sample size estimation through a formal but naïve approach assuming there are two groups to compare (instead of three, and not accounting for multiplicity). We consider (re)enrolment in school or vocational training as the primary outcome. The sample size is estimated using the following parameters: in the lived experiences survey implemented in Malawi, the proportion of pregnant or parenting adolescents who were currently out of school was 94%. In a study conducted by the Population Council in Kenya, the proportion of adolescent mothers re-entering school following an intervention comprising policy dialogue, values clarification, and advocacy ranged from 10 to 16% [32]. Given that our proposed intervention addresses the key barriers to school re-entry identified in the Population Council study, we expect a higher rate of re-entry. For this study, we shall assume that the intervention, at the minimum, will achieve a 15% absolute reduction in the proportion of adolescents not in school. The minimum total required sample size for detecting this difference between two groups for a two-sided level of significance of 10%, and statistical power of 80%, can be computed as:$$n=\frac{{[{Z}_{1-\frac{\alpha }{2}}\sqrt{2\overline{pq} }+{Z}_{1-\beta }\sqrt{{p}_{1}\left(1-{p}_{1}\right)+{p}_{2}\left(1-{p}_{2}\right)}]}^{2}}{{({p}_{1}-{p}_{2})}^{2}}$$$${p}_{1}$$ is the proportion of pregnant or parenting adolescents who will be out of school in the intervention groups; $${p}_{2}$$ is the proportion for the arm receiving only the mothers club.; $$n$$ is minimum sample size per arm;$$\overline{p }=\frac{{p}_{1}+{p}_{2}}{2}$$, and$$\overline{q }=1-\overline{p }$$. Assuming a refusal or non-consent or attrition rate of 15% and a design effect of 1.1 due to possible clustering of adolescents from the same enumeration area (EA), the required sample size for detecting a difference between the control arm (group receiving only mother club membership) and one intervention arm is 90 adolescents per arm. In this pilot study with three arms, a total sample size of 270 adolescent mothers is needed.

We will select adolescent mothers using multi-stage sampling. In the first stage, we will select EAs from the primary sampling frames developed by the National Statistical Office for the 2018 Population and Housing Census in Malawi, and by the Burkina Faso’s Institut National de la Statistique et de la Démographie in 2006 and updated in 2017. In selecting the enumeration areas, we will consider the availability of childcare centers and venues to host the adolescent mothers’ clubs. In the second stage, we will conduct a household listing in the selected EAs to identify households with eligible participants. In households with eligible adolescents, we will randomly select one using a Kish grid. The adolescents identified will be invited to participate in the baseline and endline surveys and the intervention.

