**Methods:**

We will conduct a baseline survey among adolescent mothers aged 10–19 years (N = 270, per site) enrolled following a household listing in select enumeration areas in each site. Adolescent mothers will be interviewed using a structured survey adapted from a previous survey on the lived experiences of pregnant and parenting adolescents in the two sites. Following the baseline survey, adolescent mothers will be individually randomly assigned to one of three study arms: arm one (adolescent mothers’ clubs only); arm two (adolescent mothers’ clubs + subsidized childcare), and arm three (adolescent mothers’ clubs + subsidized childcare + cash transfer). At endline, we will re-administer the structured survey and assess the average treatment effect across the three groups following intent-to-treat (ITT) analysis, comparing school or vocational training attendance during the intervention period. We will also compare baseline and endline measures of SRH and mental health outcomes. Between the baseline and endline survey, we will conduct a process evaluation to examine the acceptability and feasibility of the interventions and to track the implementation of the interventions.

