### Study sites

The study will be conducted in urban settings in Ouagadougou (Burkina Faso) and Blantyre District (Malawi). We selected these settings given previous research showing low school enrollment among pregnant and parenting adolescents. In a survey conducted in Ouagadougou, Burkina Faso, 82% of pregnant and parenting adolescents were out of school, with 23% reporting that they dropped out of school because of pregnancy [19]. Among those out of school in Burkina Faso, 39% wanted to return to school, while 79% wanted to have an income generating activity. Girls reported the lack of childcare support, stigma, and inadequate support as some of the barriers to school re-entry.

A similar survey conducted in Blantyre District in Malawi found that poverty, sexual violence, inequitable gender norms, and lack of access to accurate contraceptive information and services make girls vulnerable to early and unintended pregnancy [4]. Most girls get pregnant outside of marriage and consequently face social exclusion from their peers, parents and communities. While most rely on their parents to provide for them and their babies, some depend on their partners. However, most face dire financial situations, sometimes lacking food and other basic needs. Approximately 94% of adolescents surveyed were out of school, and about half of them dropped out because of pregnancy. However, 76% of them wanted to return to school if provided with financial and childcare support, while 93% wanted to learn vocational skills [4].

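### The 80% power behind 90 mothers per arm uses Malawi's 94% out-of-school rate only; at the protocol's own 82% for Ouagadougou, a within-site comparison has about 65%

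*Protocol article*

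**What the plan says.** Under Sample size and sample selection, the protocol article runs one two-proportion calculation. Its baseline is Malawian: "in the lived experiences survey implemented in Malawi, the proportion of pregnant or parenting adolescents who were currently out of school was 94"%. The effect is that the intervention "will achieve a 15% absolute reduction in the proportion of adolescents not in school", and the test has a "two-sided level of significance of 10%, and statistical power of 80"%. The allowances are "Assuming a refusal or non-consent or attrition rate of 15"% and a design effect of 1.1 for clustering within enumeration areas. The result is 90 per arm, and the section closes: "In this pilot study with three arms, a total sample size of 270 adolescent mothers is needed".

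The Methods part of the abstract sets the baseline survey at N = "270, per site) enrolled following a household listing", so each city gets 90 per arm.

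Study sites gives a rate for each city. For Blantyre: "Approximately 94% of adolescents surveyed were out of school". For Ouagadougou: "82% of pregnant and parenting adolescents were out of school". The Ouagadougou figure does not enter the sample size section, and no calculation for Burkina Faso is shown.

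**The concern.** The variance of a proportion grows as it moves from 94% towards 50%. A sample just large enough to detect a 15-point drop from 94% is therefore too small for a 15-point drop from 82%. The protocol holds both rates, sizes the trial on the one that needs fewer mothers, and uses the result in both cities.

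The protocol attaches an 80% power figure to 90 per arm without limiting it to Blantyre. If results are reported by city, a reader could take a null finding in Ouagadougou as fair evidence against a 15-point effect. On the protocol's own inputs, such a comparison would miss that effect about one time in three. By-site results are likely to attract attention, because the Background section says that the two countries were chosen for their contrasting school re-entry policies.

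**Working it through.** **Inputs.** Out-of-school rate in the club-only arm: 0.94 (Blantyre) or 0.82 (Ouagadougou), from Study sites. Absolute reduction 0.15, two-sided alpha 0.10 (z = 1.645), power 0.80 (z = 0.842), design effect 1.1, loss 15% and 90 per arm, all from Sample size and sample selection.

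**Formula as printed.** n per arm = [1.645·√(2·p̄·q̄) + 0.842·√(p1(1−p1) + p2(1−p2))]² / (p1−p2)², then × 1.1 and ÷ 0.85.

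**Blantyre, 0.94 against 0.79 (the plan's own case).**
- p̄ = 0.865; 2p̄q̄ = 0.23355 (root 0.4833); sum of variances = 0.2223 (root 0.4715).
- n = (0.7949 + 0.3968)² / 0.0225 = 1.4202 / 0.0225 = 63.1.
- Inflated: 63.1 × 1.1 / 0.85 = 81.7, so 82 per arm (83 if n is first rounded up to 64).

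This is below the stated 90, so the printed inputs do not return the plan's figure exactly. The difference is on the generous side. I take 90 as the planned number.

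**Ouagadougou, 0.82 against 0.67.**
- p̄ = 0.745; 2p̄q̄ = 0.37995 (root 0.6164); sum of variances = 0.3687 (root 0.6072).
- n = (1.0139 + 0.5110)² / 0.0225 = 2.3254 / 0.0225 = 103.4.
- Inflated: 103.4 × 1.1 / 0.85 = 133.7, so about 134 per arm (135 if n is first rounded up to 104), against 90 planned.

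**Power with 90 per arm.** Effective n = 90 × 0.85 / 1.1 = 69.5. Power = Φ{[0.15·√n − 1.645·√(2p̄q̄)] / √(sum of variances)}.
- Blantyre: (0.15 × 8.339 − 0.7949) / 0.4715 = 0.967, power 83%.
- Ouagadougou: (0.15 × 8.339 − 1.0139) / 0.6072 = 0.390, power 65%.

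**Ouagadougou under milder allowances.**

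| Allowance | Effective n per arm | Power for 15 points |
|---|---|---|
| 15% loss, design effect 1.1 | 69.5 | 65% |
| No loss after randomisation, design effect 1.1 | 81.8 | 71% |
| No loss, no clustering | 90 | 75% |

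**Detectable difference.** At a rate of 0.82 and effective n 69.5, power first reaches 80% at about 18.7 points. At 0.94 it does so at about 14.1 points.

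**Sensitivity to the assumed rate** (15 points, effective n 69.5): 63% at 0.80, 65% at 0.82, 73% at 0.88, 76% at 0.90, 79% at 0.92 and 83% at 0.94.

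**Both sites combined.** Assume an equal-weight, site-stratified risk difference, with 15 points in each city and the same loss and design effect.
- SE = √[(0.2223 + 0.3687) / 69.5] / 2 = 0.0461.
- 0.15 / 0.0461 = 3.25; power = Φ(3.25 − 1.645), about 95%.

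**The case against.** The strongest reply is that no by-site test is specified. Data processing and analysis speaks of an average treatment effect across the three groups and does not say whether the sites are combined. That choice may sit in an analysis plan that is not shown. If they are combined, the planned 540 mothers exceed 80% power comfortably. This stands, and it makes the shortfall conditional on a by-site comparison. It does not make the power figure right for Ouagadougou: the number was set per site and no combined calculation is given.

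A second reply is that this is a declared pilot with a calculation described as naïve, meant partly to inform a larger trial. That lowers the severity. But the naïvety is defined as comparing two groups instead of three and ignoring multiplicity, not as letting one country stand in for the other. The second objective is also comparative.

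A third reply is that 65% charges the full 15% as loss after randomisation, whereas the allowance also covers refusal and non-consent and randomisation follows the baseline survey. That is fair, and the range up to 75% reflects it. It still falls short of 80%.

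Three stronger readings are tempting but not supported:
- A reader might infer from the word total in the sample size section that 270 covers both cities. The abstract says per site, and 270 is three arms of 90.
- A reader might take the 15% as a relative reduction, which would reproduce 90 in Blantyre and lower Ouagadougou's power further. The text says absolute. How 90 was reached is a separate question.
- A reader might conclude that the whole trial is underpowered. The combined figure shows otherwise.

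**Conclusion.** The point holds for a comparison within Ouagadougou. On the protocol's formula and inputs, 90 per arm gives about 65% power for a 15-point reduction from 82%, and at most 75% with no loss and no clustering. About 134 per arm would be needed, or a difference of about 18.7 points. The stated 80% holds for Blantyre, at about 83%.

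This takes each survey rate as the club-only arm's rate at endline, as the protocol does with 94%. Both are proxies. The surveys included pregnant girls, whom the trial excludes, and the primary outcome counts school or vocational training at any time over 12 months. With 15 points held fixed, the club-only rate would have to lie above 92% for 90 per arm to give 80% power under the full allowances.

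This is a fault in the assumption behind the power figure, not in the trial's validity. Severity is moderate.

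**What to change.** In Sample size and sample selection:
- State that the 80% calculation uses the Malawi rate and applies to Blantyre (about 83% at 90 per arm).
- Give Ouagadougou's power as about 65% for 15 points, with a detectable difference of about 18.7 points at 80% power.
- Note that both survey rates are proxies for the club-only arm.
- Write 270 per site, 540 in total (2 × 270), so that this section agrees with the abstract at a glance.

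If the analysis plan combines the sites, state the power of the site-stratified comparison separately (about 95% for 15 points in each city). Whether the combined or the by-site estimate is primary is the sponsor's choice. A combined estimate averages over two policy settings that were chosen because they differ.

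The cost is a few sentences and no extra participants. The downside is a less favourable stated figure for Ouagadougou.

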Given the potential for contamination, we will not test a community wide intervention. However, we will conduct community dialogues aimed at engaging a variety of community members including community and religious leaders, health workers, social workers, teachers, and parents. The goal of these community dialogues will be to identify the root causes of adolescent pregnancies, including gender norms; to discuss possible ways to support parenting adolescents, including addressing stigma against pregnant and parenting adolescents; and to develop a sense of ownership in collectively supporting these adolescents.

While our interventions do not address societal level factors, our research uptake activities will focus on promoting laws (including community by laws) and policies that support parenting adolescents to realize their rights, including their rights to education and comprehensive SRH interventions. Figure 1 summarizes our theory of change.

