### Outcomes

#### Primary outcome

The primary outcome of this study is (re)entry or (re)enrolment in school or vocational training. At baseline, all participants will respond to a question on current school and vocational training enrolment and their intention to return to school or vocational training. At endline, participants will be asked whether they have attended school or vocation training at any time after the baseline. The primary outcome will be a binary variable coded 1 “Yes” or 0 “No” indicating whether or not the participant was enrolled in school or vocation training during the 12-month long intervention period.

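### The sample size uses a one-time, school-only rate from Malawi as the control rate for a 12-month outcome of school or vocational training, so the 80% power per site is not supported

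*Protocol article*

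**What the plan says.** The section on sample size and sample selection names (re)enrolment in school or vocational training as the primary outcome, then defines both proportions in its formula as proportions out of school. The only value it offers for the comparison arm is from the Malawi survey: "the proportion of pregnant or parenting adolescents who were currently out of school was 94" per cent. The assumed effect is that the intervention "will achieve a 15% absolute reduction in the proportion of adolescents not in school". The calculation is made "for a two-sided level of significance of 10%, and statistical power of 80" per cent. Inflation is described as "Assuming a refusal or non-consent or attrition rate of 15% and a design effect of 1.1", and the result for the comparison of the clubs-only arm with "one intervention arm is 90 adolescents per arm", or 270 for three arms. The abstract makes clear that 270 is the number per site.

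The primary outcome section defines a binary variable for "whether or not the participant was enrolled in school or vocation training during the 12-month long intervention period". The endline question asks about attendance at any time since baseline.

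The study sites section gives 82% out of school in Ouagadougou. The eligibility and exclusion lists contain no rule against mothers who are already enrolled.

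The sample size section also cites a Kenyan study in which school re-entry "following an intervention comprising policy dialogue, values clarification, and advocacy ranged from 10 to 16" per cent.

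**The concern.** The planning rate and the outcome measure different things. The planning rate is current school status at one moment, and vocational training is not part of it. The outcome is a success if the girl is in school or in vocational training at any time over 12 months. For the same girls, a second route to success and a longer window cannot make success rarer, so both differences push the control rate above the 6% point prevalence.

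The second site adds to this. The article's own survey puts 18% in school in Ouagadougou before vocational training or the 12-month window is counted, yet that site has the same 270 participants. Because enrolled mothers are not excluded, those in school at baseline could be coded as successes in any arm.

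For a fixed absolute difference, the binomial variance grows as the control rate moves from 6% towards 50%, so the same number per arm gives less power. A reader who relies on the printed 80% could take a null result at one site as stronger evidence of no effect than it is. The article also wants the pilot data to size a later trial, so the rate that describes the actual outcome should be visible.

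**Working it through.** **Inputs from the article.** Two-sided α = 0.10 (z = 1.645); power 80% (z = 0.842); out of school p₂ = 0.94 in the clubs-only arm and p₁ = 0.94 − 0.15 = 0.79 in an intervention arm; 15% loss; design effect 1.1; 90 per arm per site.

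**1. The plan's own figure.** The article's formula is n = [z₁₋α/₂ √(2p̄q̄) + z₁₋β √(p₁q₁ + p₂q₂)]² / (p₁ − p₂)².

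- p̄ = 0.865, so √(2p̄q̄) = 0.4833 and √(p₁q₁ + p₂q₂) = 0.4715.
- n = (1.645 × 0.4833 + 0.842 × 0.4715)² / 0.15² = (0.795 + 0.397)² / 0.0225 = 63.1, so 64 per arm.
- Inflated: 64 × 1.1 / 0.85 = 82.8, so 83 per arm.

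The stated 90 is not reproduced exactly, but it is a little more than the inputs require. The point made here does not depend on that gap.

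**2. Power with 90 per arm.** Effective n = 90 × 0.85 / 1.1 = 69.5 per arm. Power = Φ{[0.15 √69.5 − 1.645 √(2p̄q̄)] / √(p₁q₁ + p₂q₂)}, where 0.15 √69.5 = 1.251.

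- Control 6%: (1.251 − 0.795) / 0.4715 = 0.967, power 83%.
- Control 10%: (1.251 − 0.884) / 0.5268 = 0.697, power 76%.
- Control 16%: (1.251 − 0.986) / 0.5902 = 0.448, power 67%.
- Control 18%: (1.251 − 1.014) / 0.6072 = 0.390, power 65%.

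Power passes below 80% at a control rate of about 7.5%.

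**3. What each control rate would require, and pooled power.** Enrolment per arm for 80% power is n × 1.1 / 0.85. The detectable difference is solved numerically at effective n = 69.5. Pooled power uses 180 per arm (effective n = 139.1) with the same loss and design effect.

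| Control rate | Basis | Power per site, +15 points | Enrolled per arm for 80% | Detectable difference at 80% | Power if two sites pooled |
|---|---|---|---|---|---|
| 6% | Malawi, in school | 83% | 83 | 14 points | 98% |
| 10% | lower end, Kenyan re-entry (indicative) | 76% | 103 | 16 points | 95% |
| 16% | upper end, Kenyan re-entry (indicative) | 67% | 127 | 18 points | 91% |
| 18% | Ouagadougou, in school | 65% | 135 | 19 points | 89% |

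**4. Sensitivity to the loss assumption.** The article's 15% covers refusal as well as attrition, and refusal before randomisation would not reduce the 90. If all 90 per arm gave endline data (effective n = 90 / 1.1 = 81.8), power would be 82% at 10%, about 73% at 16% and 71% at 18%. The Ouagadougou rate still falls short.

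**The case against.** Several parts of the opposing case stand.

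- **The Kenyan rate is not a clubs-only rate.** The article cites it as a post-intervention benchmark and expects its own interventions to do better. A reader might infer that, because "we will conduct community dialogues aimed at engaging a variety of community members" is also planned here, every arm receives something like the Kenyan package and 10–16% becomes the control rate. Nothing in the article equates the two, so the range is indicative only.
- **The effect may not stay at 15 points.** The article calls 15 points a minimum, and 93% of the girls surveyed in Malawi wanted vocational skills. A broader outcome could widen the difference as well as raise the control rate. With an 18-point difference, power would be 86% at a 10% control rate and about 80% at 16%. In the other direction, if the intervention rate stayed at 21% while the control rate rose to 10%, power would be 56%.
- **The shortfall is per site.** The article does not say whether effects are estimated by site. Pooled, power stays above 80% throughout the range examined. However, 90 per arm leads to the 270 stated per site, and no power is claimed from pooling.
- **One population difference has no known direction.** The surveys included pregnant girls and the trial excludes them, but no separate enrolment rate for mothers is given.
- **It is a pilot and the calculation is called naïve.** This lowers the consequence. The article explains the word, though, only by the two-group simplification and the lack of a multiplicity adjustment. It does not qualify the control rate.

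**Conclusion.** The mismatch is real and worth correcting. The planning rate is a Malawi point prevalence for school only, while the outcome is 12-month enrolment in school or vocational training. The article's own Ouagadougou figure is three times the implied 6%. Per-site power is 83% at the planning rate and 65–76% for control rates of 10–18%, with detectable differences of about 16–19 points.

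These figures assume a fixed 15-point difference, 15% loss after randomisation, a design effect of 1.1 and analysis by site. The Ouagadougou 18% is also a point prevalence for school in pregnant and parenting girls, so it too is only a proxy.

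A reader might go further and conclude that the trial misses its 80% power, or that the article's evidence makes 6% a firm floor for the clubs-only arm. The document does not support either statement flatly: the true 12-month rate with clubs only is not given, the effect could be larger, and pooling would restore power. What can be said is that the single 80% claim is unsupported for the outcome to be analysed, and for Ouagadougou in particular.

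**What to change.** Restate the calculation for the outcome as defined: neither in school nor in vocational training at any time in the 12 months, in the clubs-only arm. Use a range of control rates that includes the Ouagadougou 18%, and label the Kenyan 10–16% as indicative. In place of the single 80%, report per-site power (about 65–76% for control rates of 10–18%) or the detectable difference (about 16–19 points).

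If the two sites are to be pooled for the primary comparison, say so and give the pooled power (about 95% at 10% and 89% at 18%).

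The baseline enrolment question would not settle the control rate by itself, because it again gives a point prevalence before the clubs start.

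The cost is a less favourable stated figure. No extra participants are needed.
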